### **‘Main’ study: iPSC derivation and in vivo Trikafta™ treatment for 4 weeks**

We propose a clinical study of subjects with a diagnosis of NCFBE. Subjects will exhibit one disease-causing CFTR mutation and/or sweat chloride measurements of 30-60 mEq/L. Each patient will be given Trikafta™ for approximately four weeks. We will monitor clinical endpoints that include FEV1, sweat chloride, quality of life questionnaire, and weight. We will also collect cutaneous punch biopsy material from each subject so that iPSC cells can be differentiated into airway epithelial monolayers and tested for response to Trikafta™.

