The study will examine iPSC-derived airway epithelial monolayers (an *in vitro* analytic tool) as a predictive means for identifying individuals with NCFBE most likely to show respiratory benefit from Trikafta™. As part of the protocol, we will perform an open-label clinical trial of orally-administered Trikafta™ in subjects with NCFBE. Subjects will be given the Study Drug elexacaftor 100 mg/tezacaftor 50 mg/ivacaftor 75 mg (2 pills once daily in the morning) and ivacaftor (150 mg) once daily in the evening, as the FDA-registered agent, Trikafta™. Dose and schedule will be identical to what has already been FDA-approved for effective treatment of CF. Trikafta™ is not approved for use in NCFBE. Enrollment is planned at Emory University. Patients enrolled in the trial will have one disease-causing CFTR variant and/or modestly elevated sweat chloride values (30-60 mEq/L), but without clinical findings sufficient for a diagnosis of cystic fibrosis.

Human subject participation in the ‘main’ study will consist of a screening day (-28), day 1 (+/- 2), day 7 (+/- 2) [phone call visit], day 14(+/-2), day 28 (+1/- 2) and day 56 (+/-2) follow up (wash-out). The visits will include patient history with concomitant medication review, physical exam, safety laboratory assessments (renal and liver panels, CBC/Diff, urinalysis), serum and urine pregnancy testing, CFTR genotype, spirometry, O2 saturation, sweat chloride test, cutaneous punch biopsy for iPSC derivation, EKG, drug accountability and questionnaire (QOL assessment), concomitant medication review, and adverse event assessment. No longer-term follow-up beyond day 56 is being planned (except for possible cutaneous biopsy by day 70 if needed (see below).

We anticipate the screening and enrollment visit will require 4-6 hours to complete the informed consent, medical history, O2 saturation, concomitant medication review, physical exam, safety laboratory assessments (CBC/Diff, RENAL/LFT chemistry panel, and urinalysis),

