**Protocol Title: Evaluating Trikafta for the treatment of patients with non-cystic fibrosis bronchiectasis (NCFBE)**

---

EKG, CFTR genotyping, questionnaire, serum pregnancy test for females, sweat chloride test, and spirometry.

On day 1 (when subject returns), the visit will require approximately 6 hours to complete the concomitant medication review, adverse event assessment, interval medical history, physical exam, O2 saturation, safety laboratory assessments (CBC/Diff, RENAL/LFT chemistry panel, and urinalysis), questionnaire, sweat chloride, urine pregnancy test for females, spirometry, cutaneous punch biopsy (3mm), drug dispensing, and drug administration. The cutaneous punch biopsy may occur at any time between the Screening Visit and Day 1 based on dermatology clinic schedule availability.

- 1 Cutaneous 3 mm punch biopsy (performed here (and on day 56 (or up to two weeks later) if necessary to produce additional iPS cells)): In this procedure, a circular blade is rotated from epidermis to subcutaneous fat, yielding a ~ 3 mm cylindrical core of tissue. Extending the skin perpendicular to the incision line allows for facile closure, which can typically be accomplished with a single suture. Pain is well-managed by local subcutaneous anesthetic. A small fibrotic scar can be minimized by linear closure of the biopsy. Significant pain, bleeding, or infection are very rare.

The subject will complete a phone call visit on day 7 (+/-2) that will require approximately 30 minutes to complete concomitant medication review, interval medical history, and adverse event assessment.

On day 14 (+/-2) the subject will return for a visit that will require approximately 4-6 hours to complete concomitant medication review, interval medical history, adverse event assessment, physical exam, drug dispensing and drug return, questionnaire, safety laboratory assessments (CBC/Diff, RENAL/LFT chemistry panel, and urinalysis), sweat chloride test, EKG, O2 saturation and spirometry.

On day 28 (+1/-2) we will conduct interval medical history, adverse event assessment, concomitant medications, physical exam, sweat chloride test, spirometry, O2 saturation, safety laboratory assessments (CBC/Diff, RENAL/LFT chemistry panel, and urinalysis), questionnaire, and drug return. This visit should require 4-6 hours to complete. This visit should occur no later than Day 29 since a 28-day supply of Trikafta™ will be provided.

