The 'wash-out' visit will be conducted on day 56 (+/-2) which will require approximately 4-6 hours to complete concomitant medication review, interval medical history, adverse event assessment, physical exam, safety laboratory assessments (CBC/Diff, RENAL/LFT chemistry panel, and urinalysis), questionnaire, sweat chloride, urine pregnancy test for females, cutaneous punch biopsy (3mm) if necessary to obtain additional cells, O2 saturation, and spirometry. The cutaneous punch biopsy may occur within  $\pm$  14 days of the day 56 visit based on dermatology clinic schedule availability. No further data will be collected after all study procedures and measurements are completed.

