| LB = Lower Bound, UB = Upper Bound
Note: Thirty total patients will be enrolled in the unlikely event that a subject discontinues participation (e.g., due to elevated liver function tests, skin rash, or for other reasons). |                                   |                                                                                      |                                       |

With a sample size of 16 (29) participants, we anticipate a 97% (>99%) power to detect a mean sweat chloride decrease of 10 mmol/L assuming a standard deviation of 9.7 mmol/L (Boyle, Bell et al. 2014, Vermeulen, Le Camus et al. 2017) under a two-sided 0.05 alpha-level paired t-test. With a higher standard deviation of 15 mmol/L, the power decreases to 70.3% (93.4%) to detect a mean decrease of 10, but we retain 96.2% (>99%) power to detect the hypothesized mean decrease of 15 mmol/L with a sample size of 16 (29) patients.

SAEs and AEs will be tabulated using standard coding terms sorted by System Organ Class (SOC). The incidence of AEs will be tabulated by seriousness and severity. The number of SAEs and AEs will be summarized as follows: (i) The proportion of subjects with at least one (S)AE, (ii) The average number of (S)AEs per subject, and (iii) The rate of (S)AEs per subject week of follow-up.

**Expected Outcomes** Subjects will be recruited by study investigators as above. Please note that based on considerable past experience conducting clinical trials and past collaborations with NCFBE clinical leadership throughout the US, we do not have concerns regarding our ability to perform the patient-oriented study described here, or to propagate and characterize iPS cells (Crane, Kramer et al. 2015, Mou, Brazauskas et al. 2015, Hawkins, Kramer et al. 2017, Jacob, Morley et al. 2017). The ‘main’ study protocol will evaluate the clinical benefit of Trikafta™ in patients with NCFBE. In addition, the study will furnish one test of our hypothesis that thresholds of CFTR activity in differentiated iPS cells *in vitro* predict benefit following Trikafta™ *in vivo*. If a strong correlation can be established between Trikafta™ response *in vitro* and *in vivo* (e.g., FEV1), the clinical results will provide evidence regarding usefulness of *in vitro* models for predicting clinical efficacy in this setting.

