## **15. Withdrawal of Participants**

Criteria for discontinuing the 'main' study intervention (e.g., halting rules), may include any monitoring test(s) and associated clinical decision point(s) which in the opinion of the clinical investigators, qualified designees, or Data Monitoring Committee are viewed as placing the patient at significant risk if Trikafta™ administration is to continue. This could include, for example (but is not limited to) worsening liver function or abnormalities associated with Trikafta™ administration (see also below). Discontinuation from Trikafta™ does not mean discontinuation from the 'main' study, and remaining study procedures should be completed as indicated by the study protocol and lead investigators. If a clinically significant finding is identified (including, but not limited to changes from baseline) after enrollment, the investigators or qualified designees, and/or Data Monitoring Committee (also referred to as Data Safety Monitoring Committee, DSMC) will determine whether any change in participant management is needed. Any new clinically relevant adverse finding will be reported as an adverse event (AE).

The data to be collected at the time of 'main' study intervention discontinuation will include:

- All measurements described for the day 56 follow-up/washout visit

Participants are free to withdraw from participation at any time upon request.

An investigator may discontinue or withdraw a participant from the study for the following reasons:

- If any clinical adverse event, laboratory abnormality, or other medical condition or situation occurs such that continued participation in the study would not be in the best interest of the participant
- Disease progression which requires discontinuation of the 'main' study intervention
- If the participant meets an exclusion criterion (either newly developed or not previously recognized) that precludes further study participation
- Participant is unable to receive Trikafta™ for 3 days
- Pregnancy
- Significant study intervention non-compliance

The reason for participant discontinuation or withdrawal from the 'main' study will be recorded. An attempt will be made to replace subjects who sign the informed consent form and receive Trikafta™, and subsequently withdraw, or are withdrawn or discontinued from the study.

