Once the four-week treatment period is complete, participants will no longer receive Trikafta™. There is a chance that the NCFBE will improve when taking Trikafta™. However, NCFBE symptoms may appear to worsen after the participant stops taking Trikafta™ as respiratory function returns to baseline.

Women:

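### The adverse event summaries pool about four weeks on drug with about four weeks off drug, so the rate per subject-week does not estimate how often events occur on Trikafta

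*Protocol*

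**What the plan says.** Under Sample size, Section 7 lists three AE and SAE summaries: the proportion of subjects with at least one event, the average number of events per subject, and "The rate of (S)AEs per subject week of follow-up". Events are also tabulated by system organ class, seriousness and severity. Earlier in Section 7, safety endpoints are to be given as counts and percentages or means and standard deviations. No part of the protocol defines an on-treatment window or splits events by period.

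On exposure, the main-study objectives in Section 2 state: "Each patient will be given Trikafta™ for approximately four weeks". Section 6 asks that the Day 28 visit be no later than Day 29, "since a 28-day supply of Trikafta™ will be provided", and Section 16 says: "Once the four-week treatment period is complete, participants will no longer receive Trikafta™".

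On follow-up, the schedule in Section 6 marks AE assessment at Days 1, 7, 14, 28 and 56, and the text adds: "No longer-term follow-up beyond day 56 is being planned". Section 15 provides that "Discontinuation from Trikafta™ does not mean discontinuation from the 'main' study". The same section also lets the investigator withdraw a participant from the study, for example for an adverse event or after 3 days without drug.

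**The concern.** Verifying safety is a secondary objective in Section 4, in a population for which the drug is not approved and with no control arm. The natural safety question is how often events occur while patients take the drug. A second, separate question is what happens after they stop.

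The protocol treats these as different risks. Section 16 warns that "symptoms may appear to worsen after the participant stops taking Trikafta™". The monitoring table in Section 21 expects the known toxicities to resolve, as a rule, once drug is withdrawn. A rate over all follow-up merges the two periods and answers neither question.

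The efficacy analyses in Section 7 do keep the periods apart. Longitudinal FEV1 and the secondary endpoints are summarised through Day 28, and the mixed models carry Day 28 and Day 56 as distinct time points. Section 20 says the data should help guide larger studies, and an interpretable on-drug rate would be useful for those.

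**Working it through.** The protocol states no AE rate and no person-time total, so there is no figure to reproduce. The check is person-time arithmetic.

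**Inputs**
- Time on drug: 28 days (Sections 2, 6 and 16).
- End of follow-up: Day 56 (Section 6). I take follow-up to run from Day 1 to Day 56.
- Visit windows in the Section 6 text: Day 28 (+1/-2), hence Day 26 to 29; Day 56 (±2), hence Day 54 to 58.
- Subjects: 29 (Section 7).
- r, the off-drug to on-drug event rate ratio: not in the protocol, so a range is shown.

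**Step 1: share of follow-up off drug**
- As planned: 1 − 28/56 = 50%.
- Lowest across the windows: 1 − 29/54 = 46%.
- Highest across the windows: 1 − 26/58 = 55%.
- In subject-weeks: 29 × 8 = 232 in total, of which 29 × 4 = 116 are on drug.

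**Step 2: pooled rate against on-drug rate**

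Let a be the on-drug rate per week. Then pooled rate = (4a + 4ra)/8 = a(1+r)/2.

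| Assumed r | Pooled rate / on-drug rate |
|---|---|
| 0 | 0.50 |
| 0.25 | 0.625 |
| 0.5 | 0.75 |
| 0.75 | 0.875 |
| 1 | 1.00 |
| 1.5 | 1.25 |
| 2 | 1.50 |

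As an illustration with an assumed count, take 29 on-drug events.
- On-drug rate: 29/116 = 0.250 per week.
- Pooled rate with no off-drug events (r=0): 29/232 = 0.125.
- Pooled rate with 58 off-drug events (r=2): 87/232 = 0.375.

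The same on-drug experience therefore gives a reported rate anywhere from half to one and a half times the on-drug rate over this range of r.

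**Step 3: the other two summaries**

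The proportion with any event and the mean number per subject are not divided by time. Adding wash-out events can only raise them or leave them unchanged. They mix the periods but are not diluted.

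**Step 4: early stoppers**

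A subject who stops at Day 14 and completes Day 56 is off drug for 1 − 14/56 = 75% of follow-up. One who stops after week 1 and completes is on drug for 1 week of 8. The effect on the cohort is small: one such week-1 stopper among 29 moves on-drug time from 116/232 = 50.0% to (116 − 3)/232 = 113/232 = 48.7%.

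**Step 5: where on-drug time ends**

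The schedule table in Section 6 marks study-drug administration at Day 28. The text for that visit lists drug return and no administration. An on-treatment window cannot be fixed cleanly until the two are reconciled.

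**The case against.** The strongest reply is that the rate is correctly labelled. It is a rate over follow-up, which is a legitimate quantity, and the schedule lets any reader see that half of it is off drug. It is purely descriptive: no test, comparison or stopping rule uses it. The data monitoring committee reviews safety data throughout, and stopping for an individual rests on clinical judgement. On-treatment windows and table layouts are often left to an SAP, which is not shown here. All of this stands and lowers the severity. It does not remove the point, because Section 7 itself chooses the denominator, and that denominator cannot give the on-drug frequency.

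Three stronger readings are tempting, and the protocol does not support them.
- *The on-drug rate is understated by 25% to 50%.* This holds only if r lies between 0 and 0.5. The expectation in Section 21 that toxicity resolves off drug favours a low r for drug-related events. The summary counts all events, however, including background disease, and the worsening foreseen in Section 16 could take r above 1.
- *All three summaries hide on-drug harm.* Only the rate can be diluted.
- *Everyone who stops early for toxicity adds many off-drug weeks.* Section 15 allows continued follow-up but also allows withdrawal, and it has the Day 56 measurements taken when drug is discontinued. Long off-drug follow-up is therefore possible but not assured, and Section 7 regards discontinuation as unlikely.

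**Conclusion.** The point holds as one of interpretability. About half of the planned person-time is off drug, and none of the three summaries separates the periods. The pooled rate is (1+r)/2 times the on-drug rate, so it equals the on-drug rate only if event rates are the same in both periods. Over assumed r from 0 to 2 it runs from 0.50 to 1.50 times the on-drug rate. Because the protocol gives no r and its own statements point both ways, the direction and size of the distortion are uncertain. What is certain is that the rate as written does not estimate on-drug AE frequency. These figures assume full follow-up to Day 56 and 28 days of drug; early stoppers who stay in the study would add off-drug time. Severity is low, since nothing is decided on this measure.

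**What to change.** In Section 7 (Sample size, AE summaries):
- Report each AE and SAE summary for a pre-stated on-treatment period and for a post-treatment period to Day 56, assigning events by onset date.
- Divide each period's events by the subject-weeks actually spent in that period, using actual last-dose dates.
- Keep the whole-study figures as an additional line.

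In Section 6, reconcile the schedule table's study-drug administration mark at Day 28 with the visit text, so that the end of on-drug time is unambiguous.

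The cost is wording and table layout. AE assessment and drug accountability are already scheduled, so no visit or procedure is added. The downsides are less person-time behind each rate (about 116 subject-weeks per period instead of 232 in total) and an on-drug rate that may look less favourable than the pooled one.

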## **8. Data and/or Specimen Banking**

- Patient skin biopsies and iPSCs derived from skin samples will be anonymized (identifiable only by a patient-specific identification number). The frozen iPSCs will be maintained in liquid nitrogen at the University of Texas, Houston by collaborating laboratories for two years after completion of the study, and then destroyed. Investigators conducting laboratory tests of iPSCs and primary airway epithelium will have access to specimens but will not have access to patient names or identifiers. This approach will be approved by the University of Texas at Houston IRB.
- Data for each subject (Section 6) will be maintained in patient-specific study folders in anonymized fashion (as above) and stored in a locked and secure cabinet in a limited access study room. Patient data maintained as computer files will be password protected and maintained on a limited access, user specific network drive. All patient data specific to the study will be kept for two years after trial completion and then destroyed.
- Links between patient identification numbers and study subject data will be kept in a secure password protected computer file by project leadership ([name] and [name]) and made available to other study personnel as deemed necessary.
- Participant confidentiality and privacy will be strictly held in trust by the participating investigators, their staff, and others responsible for the intended interventions. This confidentiality is extended to cover testing of biological samples and other tests in addition to the clinical information relating to participants. Therefore, the study protocol, documentation, data, and all other information generated will be held in strict confidence. No confidential information concerning the study, or the data will be released to any unauthorized third party without prior written approval. Study personnel will have access to sources of information regarding participants as delineated by the informed consent document signed by all study subjects.
- All research activities will be conducted in as private a setting as possible.
- The clinical investigators, other authorized representatives, representatives of the Institutional Review Board (IRB), or regulatory agencies may inspect all documents and records required to be maintained by the investigators, including but not limited to, medical records (office, clinic, or hospital) and pharmacy records for the participants in this study. The clinical study site will permit access to such records.
- The study participant's contact information will be securely stored at each clinical site for internal use during the study. At the end of the study, all records will continue to be kept in a secure location for as long a period as dictated by the reviewing IRB, Institutional policies, or other requirements (currently planned for two years post-study completion).
- Study participant research data, which is for purposes of statistical analysis and scientific reporting, will be transmitted and stored securely as above. This will not include the participant's contact or identifying information. Rather, individual participants and their research data will be identified by a unique study identification number. The study data entry and study management systems used by clinical research staff will be secured and

password protected. At the end of the study, all study databases will be de-identified and archived by the PI. With regard to other patient related aspects of confidentiality, all interviews and procedures will be held in a private room.

## **9. Sharing of Results with Participants**

**Sharing of information with study participants and others** Subjects enrolled in the study will have access to their study information once participation in the trial is complete. In addition, study data may be provided to the patient's pulmonary (or other) physician, if desired by the study subject. This is important, since patients enrolled in our trial who exhibit a favorable response to one month of Trikafta™ treatment are likely to benefit from continued therapy. Because the drug is expensive (~ \$300,000/year) and not "on label" for NCFBE, third-party payers may not reimburse for Trikafta™ treatment. Patients and their physicians, however, can sometimes use data as provided in our protocol to gain third-party approval for Trikafta™ reimbursement, indicating the importance of making participant data available as intended here.

### **Reporting of Study Results**

De-identified data from this study, including de-identified genetic information, may be shared with the research community at large to advance science and health. Any personal information that could identify an individual study subject will be removed or coded before that information is shared with the research community. This will ensure that, by current scientific standards and known methods, it is extremely unlikely that anyone would be able to identify a study subject from the information we share. Despite these measures, it is not possible to guarantee anonymity of personal data.

